Recruitment will take place in the Eastern Clinical Research Network (National Institutes of Health Research) region of the UK and in the Beijing and Tai’an cities, China. In the UK, recruitment has started in January 2021 and will be undertaken by approximately 10–15 general practioner (GP) practice. A random computer selection of participants living in the designated postal code areas meeting the age criterion and having ≥1 known dementia risk factor according to the GP registry will be approached through an information letter, inviting them to contact the local study centre. In China, participants will be recruited from seven hospitals through advertisements on hospital websites, targeted recruitment via local social media (WeChat) or direct approach by nurses and physicians. In China, recruitment is expected to start mid-2021.

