### Primary and secondary outcomes

Following a type II hybrid design, primary outcomes for effectiveness and implementation are equally important. The primary effectiveness outcome is the change in the Cardiovascular Risk Factors, Ageing and Incidence of Dementia (CAIDE) dementia risk score between baseline and 18-month follow-up.^31^ The main secondary effectiveness outcomes include change in the individual modifiable components of the primary outcome, change in ten-year cardiovascular disease (CVD) risk, cost-effectiveness and certain clinical outcomes such as incidence of mild cognitive impairment (MCI) and dementia. The operationalisation of all effectiveness outcomes is listed in table 1.

**Table 1 T1:** Effectiveness outcomes

Primary outcome	Points
CAIDE Score (range: 0–15), which is composed of and calculated from the following:	
Age	
<47 years	0
47–53	3
>53	4
Education	
≥10 years	0
7–9 years	2
<7 years	3
Gender	
Female	0
Male	1
Systolic blood pressure	
≤140 mm Hg	0
>140 mm Hg	2
BMI	
≤30 kg/m^2^	0
>30 kg/m^2^	2
Total cholesterol	
≤6.5 mmol/L	0
>6.5 mmol/L	2
Physical activity*	
Yes	0
No	1

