### Protocol adjustments due to COVID-19 pandemic

As a result of the COVID-19 pandemic and related local research restrictions, certain adjustments have been made to the original study protocol as published on the International Standard Randomised Controlled Trial Number Register (ISRCTN). First, recruitment was planned to start in early 2020 but had to be suspended until January 2021. Second, as it is difficult to predict the development of the pandemic and associated restrictions, we have slightly amended the study protocol to allow for flexible measurement procedures at baseline that can be operationalised in either one or two face-to-face visits and for a flexible intervention duration of 12–18 months. However, we will strive for a follow-up period of 18 months in as many participants as possible.

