### Statistical analysis

#### Sample size

The CAIDE Score will be used as primary effectiveness outcome. We decided to use a difference of 0.186 points on the CAIDE Score between the average of both study groups as a minimum target threshold, because this difference was observed in the Prevention of Dementia by Intensive Vascular Care trial after 2 years (p=0.005; intervention group=−0.290±1.47 SD and control group=−0.104±1.36 SD). Attrition after 2 years of follow-up was 21% in this study.^14^ With 80% power, a 0.05 two-sided significance level, accounting for 21% attrition, and a mean difference in change in CAIDE of 0.186, the required sample size is estimated to be 2319 participants. To allow for unexpected factors, we raised this to 2400.

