#### Data analysis

The effect on the CAIDE Score will be analysed using linear mixed-effect models according to the intention-to-treat principle, taking clustering within partner pairs and country into account by testing best fit for random intercept and/or slope. If needed, we will adjust for baseline imbalances and take clustering of the intervention within centre and/or coach into account. No imputation of the CAIDE Score will be done for the primary analysis. In sensitivity analyses, we will use multiple imputation to assess the impact of missing items needed to calculate the CAIDE Score, provided there are no indications that the variables are missing not at random, and a per-protocol analysis for those adherent to the intervention will be performed. Moreover, we will explore the interaction of intervention duration with the effect of the invention by adding an interaction term (intervention duration*randomisation group) to the main model. This will give insight into the potential additional intervention effect in participants with a follow-up time of less than 18 months.

Subgroup analyses will be performed for country, sex, age group, having a history of CVD, number of risk factors, willingness to change lifestyle (assessed with one question during the baseline visit), participation with(out) a participating partner, having the same coach during the full length of the study and the number of goals set. For all these factors, interaction terms will be included to test for between-subgroup differences in intervention effects.

The effect on individual modifiable components of the CAIDE Score and 10-year CVD Risk Scores will be analysed using linear mixed-effect models according to the intention-to-treat principle, taking clustering within partner pairs and country into account. Self-assessment scales, which are mostly ordinal, will be regarded as linear scales if there are at least four categories and the ‘distance’ between the categories can be regarded equal. Poisson regression or zero-inflated models may be applied to distributions resembling count or zero-inflated data. The choice of the final model will be a compromise between optimal fit and interpretability of the results for a general clinical public.

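### The duration-by-group check leaves out country-by-group, so it may report a UK–China difference in effect as an effect of intervention duration

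*Protocol article*

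**What the plan says.** **Outcome.** The section Primary and secondary outcomes defines the primary effectiveness outcome as the change in the CAIDE "dementia risk score between baseline and 18-month follow-up".

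**Follow-up.** The section Protocol adjustments due to COVID-19 pandemic amends the design to allow "for a flexible intervention duration of 12–18 months", adding that "we will strive for a follow-up period of 18 months in as many participants as possible". The outcome definition was not reworded to match.

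**Duration analysis.** The Data analysis section explores effect by duration through "adding an interaction term (intervention duration*randomisation group) to the main model". It says this will inform on participants followed for less than 18 months. No country-by-group term is named for this model.

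**Country.** The main model is a linear mixed model "taking clustering within partner pairs and country into account by testing best fit for random intercept and/or slope". Country is also one of the listed subgroup factors: "For all these factors, interaction terms will be included to test for between-subgroup differences in intervention effects". That is a separate analysis from the duration model. Randomisation is 1:1, stratified by country.

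**Timing.** UK recruitment started in January 2021. "In China, recruitment is expected to start mid-2021" (Study population and recruitment).

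**The concern.** Arm is randomised; duration is not. A duration-by-group coefficient compares the treatment effect in people with shorter follow-up with the effect in people with longer follow-up, and those groups may differ in other ways. Country is the obvious candidate.

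- **Duration may differ by country.** The starts are staggered by about half a year, and the flexibility was introduced because of the pandemic and local restrictions, which need not be the same in both places.
- **The effect may differ by country.** The UK enrols people of low socioeconomic status and China people of any status. The obesity criterion is a BMI of at least 28 in China and at least 30 in the UK, while CAIDE gives points for BMI only above 30. The sponsor plans a country subgroup test, so it regards a difference as possible.

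If both hold, a UK–China difference in effect could be read as evidence that longer use works better or worse. That reading would bear on how long the intervention should be offered.

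A smaller matter accompanies this. The outcome is worded as an 18-month change, but some participants may have their final visit earlier. The article should say plainly that their final visit counts.

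**Working it through.** **1. The plan's own figure.** Inputs from Sample size: difference 0.186, SDs 1.47 and 1.36, 80% power, two-sided 5%, attrition 21%.

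- Pooled SD = √[(1.47² + 1.36²)/2] = 1.416.
- n per arm = 2 × [1.416 × (1.960 + 0.842)/0.186]² ≈ 910; total 1820; 1820/0.79 ≈ 2304.
- A t-test calculation with the SD rounded to 1.42 gives 916 per arm, and 1832/0.79 = 2319, as stated.

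The sample size reproduces and is not in dispute. With 2400 enrolled, completers N = 2400 × 0.79 = 1896.

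**2. What the duration term estimates when country-by-group is omitted.** Assume equal country sizes, equal arms and no true duration effect. Write effects as reductions in CAIDE, and code country 0 = UK, 1 = China. The omitted country-by-group effect is projected onto duration-by-group:

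- spurious slope per month = (effect in China − effect in UK) × cov(country, duration)/var(duration)
- cov = 0.25 × D, where D = mean duration in China − mean duration in UK
- var(duration) = W + B, where W is the average within-country variance and B = 0.25 × D²
- SE per 6 months = 6 × 2 × SD/√[N × (W + B)]; once country-by-group is added, W replaces W + B

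Shortened durations are taken as uniform on 12–18 months (mean shortfall 3 months, mean squared shortfall 12). The shares shortened and the country effects are assumptions; the documents give neither.

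**3. Moderate scenario: 10% of UK and 50% of China shortened, effects 0.286 and 0.086.**

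- Mean shortfall: UK 0.3, China 1.5, so D = −1.2.
- Variances: UK 1.2 − 0.09 = 1.11; China 6 − 2.25 = 3.75; W = 2.43; B = 0.36; total 2.79.
- Slope = (−0.20) × (−0.30/2.79) = 0.0215 per month, or 0.129 points per 6 months.
- SE = 12 × 1.416/√(1896 × 2.79) = 0.234; ratio 0.129/0.234 = 0.55.
- Rejection rate = P(Z > 1.96 − 0.55) + P(Z < −1.96 − 0.55) ≈ 8.6%.

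**4. Strong scenario: all UK at 18 months, all of China uniform on 12–18.**

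- D = −3; W = (0 + 3)/2 = 1.5; B = 2.25; total 3.75; cov/var = −0.75/3.75 = −0.20.
- SE = 12 × 1.416/√(1896 × 3.75) = 0.202.
- Effects 0.25 and 0.12: 0.13 × 0.20 × 6 = 0.156 points per 6 months (84% of the 0.186 target); ratio 0.77; rejection about 12%.
- Effects 0.30 and 0.07: 0.23 × 0.20 × 6 = 0.276 points; ratio 1.37; rejection about 28%.

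**5. Simulation.** Simulated trials with fixed country, group, duration and duration-by-group terms agree:

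| Shortened UK / China | Effects UK / China | Without country-by-group | With it |
|---|---|---|---|
| 10% / 50% | 0.286 / 0.086 | 8–9% | about 5% |
| 5% / 80% | 0.286 / 0.086 | 15.6% | 4.6% |
| none / all | 0.25 / 0.12 | 12–13% | about 5% |
| none / all | 0.30 / 0.07 | 28–29% | about 5% |
| 30% / 30% | 0.286 / 0.086 | 4.4% | 4.2% |
| 5% / 80% | 0.186 / 0.186 | 4.7% | 5.1% |

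The last two rows show that both conditions are needed.

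**6. Price of the added term.** The SE per 6 months rises by the factor √[(W + B)/W]: √(2.79/2.43) = 1.07 in the moderate scenario (0.234 to 0.250) and √(3.75/1.5) = 1.58 in the strong one (0.202 to 0.319).

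**The case against.** **Short follow-up is not tied to China.** The article gives no study end date and no rule for who is shortened. A later start shortens follow-up only if there is a common end date, and late UK recruits could be affected too. This stands: the documents support saying that duration may be confounded with country, not that it is.

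**The strong scenario is near a worst case.** It has almost nobody in China reaching 18 months, which sits badly with the stated aim of 18 months for as many as possible. This also stands. The moderate scenario gives about 9%, a modest excess.

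**Country is already handled.** The main model may carry a random country slope, and a country interaction is tested separately. This stands only in part. The article does not say which term the slope would fall on; it is kept only if it fits best, and two countries estimate a slope variance poorly. The calculations above do not include such a slope. The separate country test would alert a careful reader, but it does not correct the duration coefficient. The full analysis plan, which is not shown, may specify the joint model.

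**The analysis is exploratory.** True, and this limits the weight of the point.

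A reader might infer three stronger things that the documents do not support:

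- *That the trial is underpowered because "this difference was observed in the Prevention of Dementia by Intensive Vascular Care trial after 2 years".* The article states that origin openly and uses 0.186 as a chosen minimum target, at which 80% power is correct. A lower power needs an assumed growth of effect over time and an assumed share of early visits; neither is given.
- *That visit timing might depend on arm.* Nothing in the article suggests this, and outcome assessors are blinded.
- *That people seen before 18 months have no primary outcome.* The declared amendment and the duration analysis, read together, imply that they are analysed.

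**Conclusion.** The point holds in a limited, conditional form. The duration check, as the article specifies it, can attribute a UK–China difference in effect to duration. This requires both unequal shortening and unequal effects by country. When both hold, the false-positive rate is about 9% to 29% over the scenarios from 10%/50% shortening to full shortening in China only, with spurious slopes of 0.13 to 0.28 points per 6 months against a target of 0.186. When either is absent, the rate stays near 5%. These figures rest on assumed shares and effects, equal country sizes, SD 1.416 and 1896 completers.

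Only one exploratory coefficient is affected. The primary comparison between arms is not biased, because randomisation is stratified by country. The mismatch between the 18-month outcome and the 12–18-month window is a matter of wording to reconcile. Overall this is a cheap improvement to the analysis, not a flaw in the trial's main result.

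**What to change.** - **Duration model.** Include the duration main effect, country and country-by-group as fixed terms alongside duration-by-group, so that the duration effect is estimated within country.
- **Outcome definition.** Reconcile Primary and secondary outcomes with the COVID-19 adjustments section, so that the primary outcome is the change from baseline to the final visit within the 12–18-month window.

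**Cost.** Two fixed country terms, the duration main effect if it is not already intended, and one sentence. The duration estimate becomes less precise: its standard error rises by about 7% in the moderate scenario and 58% in the strong one. That loss reflects how little within-country information on duration there would be. Sample size and the primary analysis do not change.

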### Randomisation and blinding

After completion of the baseline assessments, participants will be individually randomised in a 1:1 ratio, stratified by country, using a central, computer-generated sequence. Participating cohabiting partners will be allocated to the same study condition. Complete blinding of participants is not possible, owing to the nature of the intervention. Participants will be informed that they will be randomised to one of two lifestyle apps, without further details. All outcome assessments will be done by an independent assessor unaware of treatment allocation.

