### Pilot study

Between December 2019 and March 2020, a 6-week pilot study was conducted in the Brighton and Sussex area, the UK. Since the main aim was to test study logistics and functionality of the intervention app, participants were randomised in a 3:1 (intervention/control) ratio. An invitation letter was sent to 600 potentially eligible patients from two GPs. The response rate was 14.8% (n=89), of whom 21 participants (3.5%) could be included. The main reasons for exclusion were not living in the designated postal code area and having <2 dementia risk factors. Participants had a median age of 69 years old, and 12 (57%) were men. Fifteen participants were allocated to the intervention group and six to the control group.

During the pilot study, 10 of 15 intervention participants set at least one goal (range: 1–8 goals). Goals were set in five domains, including physical activity, healthy diet, body weight, blood pressure and cholesterol. Six of ten participants entered goal-related measurements (range: 2–243 measurements). All intervention participants used the chat functionality to consult the coach. In total, 278 messages were sent back and forth, that is, on average three messages per intervention participant per week.

The pilot study was evaluated through qualitative sessions with the participants and coaches. The main adjustments based on the participants’ feedback included improvements to the chat functionality (allowing attachments and larger font size), simplification of the functionality to enter and view measurements, setting the first goal together with the coach and more detailed instructions for app use through an instruction video and written manual. Based on feedback from the coaches, we improved the functionalities for population management in the coach portal, including an input screen to make notes about individual participants and a functionality to send education material to (groups of) participants.

A similar pilot study will be conducted in China, to test platform functionality and study logistics in all seven participating trial centres.

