### Limitations

The study may yield some limitations. First, the optimal age range for trials on dementia risk reduction is unknown.^15^ There is a trade-off between potentially more effective treatments in midlife and the chance to detect treatment effects on cognitive outcomes in late life.^4^ As in the current study, we are assessing both a dementia risk score and clinical outcomes; we have taken a pragmatic approach, targeting individuals aged 55–75 years old^15^.

Second, change in CAIDE dementia risk score is not easily translated into incidence of dementia. However, although not specifically designed as RCT outcome measure, the CAIDE Score can detect change over time.^50^

A third potential limitation is that, owing to the nature of the intervention, blinding of the participants is only partly possible. A certain degree of contamination might occur, especially in communities that live closely together. The study logistics and intervention are designed in such a way as to limit contact between participants after randomisation.

Finally, the results of the baseline measurements will be revealed to all participants, potentially leading to treatment effects in both study conditions. Also, behaviour of participants and their treating physicians may change in both study conditions as a reaction to the awareness of being part of the study (Hawthorne effect). Both mechanisms will perhaps mask (part of) the ‘true’ contrast in dementia risk between the intervention and control condition.

For the planned health economic analyses, we will rely on economic modelling, based on the intermediate outcomes reflecting risk of dementia and CVD and assumptions on their causality with the clinical endpoints dementia and CVD, because the study is not designed nor powered to detect an effect on these clinical endpoints.

The high prevalence of dementia, lower provision of high-quality cardiovascular preventive care in LMIC and lower uptake of such programmes in Western low-SES populations require affordable and straightforward preventive strategies. If proven effective and implementable, our pragmatic smartphone intervention facilitates widespread use and reduction of dementia risk for hard-to-reach populations across the globe.

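### The age interaction is tested on grouped age although age is known for everyone; if the effect changes linearly with age, this gives up information, by an amount that depends on a grouping the article does not state

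*Protocol article*

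**What the plan says.** The Data analysis section of the protocol article names nine subgroup factors in one sentence, which begins "Subgroup analyses will be performed for country, sex, age group, having a history of CVD, number of risk factors". The next sentence fixes the method: "For all these factors, interaction terms will be included to test for between-subgroup differences in intervention effects". The test of effect modification by age is therefore treatment by age group. No interaction with age as a measured variable is stated. The only other analytic use of age is as the timescale in a Cox sensitivity analysis, which does not test effect modification.

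The inclusion criteria in Box 1 restrict age to 55-75 years, so age must be known for everyone enrolled. The article gives neither the number of age groups nor the cut-points. It refers to a full analysis plan on the trial registry, including the subgroup hypotheses, which is not shown here.

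The sample size is set for the main effect only: "With 80% power, a 0.05 two-sided significance level, accounting for 21% attrition, and a mean difference in change in CAIDE of 0.186". No power is stated for any interaction.

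**The concern.** Grouping a measured modifier treats everyone within a band as alike and ties the result to where the band edges fall. If the effect of the app rises or falls steadily over the 20-year age range, a test on groups uses less of the available information than a test on age itself. Interaction tests in a trial sized for its main effect are weak already, so the loss falls where there is little to spare: a real age gradient becomes more likely to be missed.

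The plan's own practice makes the alternative easy to adopt. In the same section, intervention duration is to enter as a product term with randomised group, with no mention of bands. Continuous age could enter the same model in the same way.

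**Working it through.** **Inputs from the article.** Target difference 0.186 ("We decided to use a difference of 0.186 points on the CAIDE Score between the average of both study groups as a minimum target threshold"). SDs of change 1.47 and 1.36 ("p=0.005; intervention group=−0.290±1.47 SD and control group=−0.104±1.36 SD"). Power 80%, two-sided 5%, attrition 21%. Planned total 2400. Allocation: "participants will be individually randomised in a 1:1 ratio, stratified by country". Age range 55-75. Pilot: "Participants had a median age of 69 years old, and 12 (57%) were men" (n = 21).

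**Assumptions.** The shape of the age distribution, its SD, the grouping, and a linear change of effect with age. The article gives none of these, so ranges are shown.

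**1. The plan's own figure.** Pooled SD = √[(1.47² + 1.36²)/2] = 1.416. Per arm, n = 2(1.96 + 0.842)² × 1.416²/0.186² = 910, so 1820 in total, and 1820/0.79 = 2304. The article states 2319, which is 0.6% higher; an SD rounded to 1.42 gives 2317. The figure is reproduced. With 2400 randomised, 2400 × 0.79 = 1896 are evaluable and main-effect power is 82%.

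**2. Information kept by grouping.** Under a linear gradient, the share kept is the between-group share of the variance of age.

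Uniform age on 55-75 has variance 20²/12 = 33.3.
- Two equal groups have means 60 and 70, so the between-group variance is 5² = 25 and 25/33.3 = 75% is kept.
- For k equal groups the share is 1 − 1/k²: 89% for three and 94% for four.
- For a cut at 70, the proportions are 0.75 and 0.25 and the means 62.5 and 72.5, so the between-group variance is 0.75 × 0.25 × 10² = 18.75 and 56% is kept.

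Normal age with a median split keeps 2/π = 64%. The truncated-normal cases were evaluated numerically.

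| Grouping | Information lost |
|---|---|
| Two groups, median split | 25% (uniform), 31-34% (truncated normal), 36% (normal) |
| Cut at 65, ages centred on 69, assumed SD 5, truncated to 55-75 | 40% |
| Cut at 60 or 70, uniform | 44% |
| Cut at 60 or 70, truncated normal | 40-90%, depending on shape and cut |
| Three equal groups | 11% (uniform) to 21% (normal) |
| Four equal groups | 6% (uniform) to 14% (normal) |

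**3. What this means for power at 1896 evaluable.** SE of the main effect = 1.416 × √(4/1896) = 0.0650. SE of the difference in effect between two equal halves = 2 × 0.0650 = 0.130. If that difference is 0.186, as large as the whole target effect, the non-centrality for two groups is (0.186/0.130)² = 2.04. Continuous age gives 2.04/0.75 = 2.73 if age is uniform and 2.04/0.637 = 3.21 if normal. With uniform age, thirds give 2.73 × 0.889 = 2.42 on 2 df, and quarters give 2.73 × 0.9375 = 2.56 on 3 df.

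| Difference between halves | Two groups | Thirds, 2 df | Quarters, 3 df | Continuous, uniform | Continuous, normal |
|---|---|---|---|---|---|
| 0.093 | 11% | 10% | 9% | 13% | 15% |
| 0.186 | 30% | 27% | 24% | 38% | 43% |
| 0.372 | 82% | 80% | 77% | 91% | 95% |

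The columns for thirds and quarters assume uniform age. Scoring thirds as an ordered trend (1 df, uniform age) gives 34% in the middle row.

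**4. The opposite case.** If the effect changes in a single step exactly at the median cut, with the same 0.186 difference, the two-group test keeps its 30%. A linear term in age has 24% (uniform) or 21% (normal).

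**The case against.** The strongest objection is that the article lists its subgroup factors in a single sentence and points to a full analysis plan that is not shown. That plan may fix the groups, score them as ordered, or fit continuous age as well. This stands as a limit on what can be claimed: the absence of cut-points is not a fault here. It does not remove the point, because grouped age is what the article states, not a detail it leaves open.

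The gain also depends on linearity and is modest. Where the interaction is as large as the whole target effect, power stays below one half under either coding; where it is half that size, the choice hardly matters. Under a step at the cut, grouping is better. All of this stands.

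Four stronger readings are tempting and not supported:

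- A reader might infer that the plan loses a quarter to two-fifths of the information whatever the groups. That range needs a two-group split, which the article never states. Its upper end comes from a cut at 65 with only about 24% of participants below it. It also borrows its centre of 69 from 21 UK pilot participants and assumes the SD.
- A reader might infer that grouping creates spurious findings. With a prespecified cut, the grouped and continuous tests have the same nominal type I error, and nothing says the cut will be chosen after seeing the data.
- The Limitations section says that "the optimal age range for trials on dementia risk reduction is unknown", which might suggest that age is the subgroup question the trial most wants answered. That sentence explains the eligibility range and does not mention the subgroup analysis.
- A reader might assume that the number of risk factors will also be banded. The article does not say so.

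**Conclusion.** The point holds as a minor and conditional one. Testing effect modification on age group rather than age is a stated choice. Under a linear gradient, every grouping examined loses information. More groups lose less, but an unordered test then spends the saving on degrees of freedom, so thirds and quarters end up no more powerful than two halves.

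For an interaction as large as the target effect, the cost is roughly 8 to 14 percentage points of power with uniform age (38% against 30% down to 24%), or about 13 points for a median split of normal age (43% against 30%). These figures rest on a linear change, an assumed age distribution, equal groups and 1896 evaluable participants. The primary analysis and the other eight subgroup factors are unaffected.

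**What to change.** State that the age interaction will be tested as treatment by continuous age, linear in the main version, with a spline to check for departure from linearity. Report the estimated effect with its confidence interval at a few chosen ages, for example 55, 65 and 75. Keep age groups for the subgroup display only. If the analysis plan on the registry already does this, the article's wording only needs to be read alongside it.

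The change costs about one line of text and needs no new data. Its price is the linearity assumption, with some loss of power if the true change is a step at the cut; the spline and the grouped display are there to reveal that.
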